## Abstract

**Background:**

Recent research indicates that patients with anorexia (AN) show specific eye movement abnormalities such as shorter prosaccade latencies, more saccade inhibition errors, and increased rate of saccadic intrusions compared to participants without AN. However, it remains unknown whether these abnormal eye movement patterns, which may serve as potential biomarkers and endophenotypes for an early diagnosis and preventive clinical treatments, start to manifest also in people with subclinical eating disorders (ED) symptomatology. Therefore, we propose a protocol for an exploratory experimental study to investigate whether participants with subclinical ED symptomatology and control participants differ in their performance on several eye movement tasks.

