## Methods/design

### Participants and procedure

A young adult female sample will be chosen due to the higher prevalence of EDs in this population [1, 2, 7]. Thus, the sample will comprise young adult women in the 18–25 age range. The sample procedure will be through public advertisements and social media posts (convenience sampling). Inclusion criteria will be: (a) normal (or corrected) visual acuity; (b) gender: women; (c) current body mass index (BMI) in the normal range according to World Health Organization (WHO) (between 18.5–24.9). Exclusion criteria: (a) self-reported lifetime history of significant brain injury, neurological condition, ocular and/or visual pathology; (b) self-reported lifetime history of an ED or other mental illness; (c) self-reported current use of psychotropic drugs (e.g., antidepressants) or intake of recreational synthetic or natural drugs; (d) incomplete data collection or eye-tracker calibration failure; (e) inability to understand Spanish; (f) out of range age. The Spanish Eating Disorder Examination Questionnaire (S-EDE-Q) [36] will be administered since it is considered the gold standard for assessment of ED pathology [37]. The EDE-Q have shown good predictive as well as concurrent validity [37, 38]. Further, has been shown good psychometric properties in young adults in Spain [36]. This tool will serve as a pre-screening tool, allowing us to split the sample into two groups of participants with subclinical ED symptomatology and control participants according to their EDE-Q score, as defined by the study criteria (see below). A global EDE-Q score ≥ 2.8 has been shown to provide an optimal trade-off between sensitivity and specificity when it is used for screening in primary care [38]. The pre-screening will allow to form two groups of similar size: once the desired participant sample size has been reached for one of the groups, only participants falling into the other group defined for the study will be invited to take part.

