### Sample size calculation

An 80% of power analysis and a significant criterion of α = 0.05 were set since these are considered a convention for general use specifically in the psychology field [41, 42]. Regarding the effect size, based on previous literature on the topic [34], we choose a large effect size (d = 0.8) [41]. Thus, a priori t-test G*Power v3.1.9.2 (Dusseldorf University, Germany, http://www.gpower.hhu.de/en.html) analysis yields a minimum sample of 26 participants in each group (N = 52, two groups: participants with subclinical ED symptomatology vs. control participants). Nevertheless, if significant results were not obtained after completion of the study, a retrospective power analysis will be carried out with the participants responses to verify whether the non-significant result is due to lack of relationship between the groups or due to lack of statistical power. In this case, more participants will be recruited.

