### Statistical analysis

Statistical analyses will be performed with SPSS v.28. Normality and outliers will be checked through graphic tests such as QQ plots, histograms, and box plots. Cronbach’s α for each questionnaire will be reported. Group analyses will be performed with Student's t-test paired comparison (for normal distribution) or Wilcoxon tests (for non-normal distribution). We will apply a correction for multiple t-test comparisons. Cohen’s d will be reported for variables showing significance. In case of significant differences between study groups, we will then include confounding variables (premorbid intelligence and anxiety) as covariates in the analysis described above. Across groups, exploratory Pearson's correlation analyses will also be conducted between S-EDE-Q, STAI scores, and BMI and the outcome measures associated with the eye-tracking data (see Table 1, for a detailed view). Additionally, if significant differences are found between STAI scores and SWJ rate, consistent with previous literature [31, 32], a discriminant analysis will be performed on the entire sample to elucidate to what extent both measures correctly classify group membership (participants with subclinical ED symptomatology vs. control participants). Alpha will be set at 0.05 for all analyses.

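### Cohen's d is planned only for significant outcomes, so the reported effect sizes will be too large on average and the other outcomes have no planned standardised effect size

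*Protocol article*

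**What the plan says.** In the protocol article, the Statistical analysis section sets out group comparisons of the eye-tracking outcomes, then states "We will apply a correction for multiple t-test comparisons", and next that Cohen's d "will be reported for variables showing significance". The section closes with "Alpha will be set at 0.05 for all analyses". It names no effect size or interval for group comparisons that miss significance.

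The Sample size calculation section gives the design: "An 80% of power analysis and a significant criterion of α = 0.05 were set", "we choose a large effect size (d = 0.8", and "a minimum sample of 26 participants in each group (N = 52, two groups". The groups are to be about equal (Participants and procedure: "The pre-screening will allow to form two groups of similar size").

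The Abstract describes the work as exploratory: "we propose a protocol for an exploratory experimental study to investigate whether participants with subclinical ED symptomatology and control participants differ". The Discussion hopes that the results will open the way to later studies.

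**The concern.** The rule makes the p-value decide whether an effect size is shown. At 26 per group only fairly large observed differences reach significance, so the published values of d would be a set cut off from below. Later teams who plan studies on those values would tend to start from effects that are too large. The authors took their own design effect from earlier literature, so this use is easy to foresee.

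The outcomes that miss significance also lose something. The Sample size calculation section wants to know whether a non-significant result reflects no relationship or too little power. A d with its confidence interval speaks directly to that question, yet the rule plans no d for exactly those outcomes.

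**Working it through.** **Inputs.** 26 per group, alpha 0.05, 80% power and d = 0.8 come from Sample size calculation. The reporting rule and the unnamed multiplicity correction come from Statistical analysis. Table 1 lists 18 outcomes by count: 1 fixation + 5 prosaccade + 7 antisaccade + 5 memory-guided.

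**Step 1: reproduce the plan's sample size.** A two-sided two-sample t-test (noncentral t) with d = 0.8, alpha 0.05 and 80% power needs n = 25.52, so 26 per group, with power 80.7%. This matches the protocol. A one-sided test would need 21 per group (20.03 rounded up) and a paired test 15 pairs (14.30 rounded up). The stated figure is therefore the two-sided, independent-groups one. That test is used below, although the analysis text speaks of a paired comparison.

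**Step 2: the smallest d that can be reported.** With equal groups, d = t × √(2/n). Significance needs |t| of at least t(0.975, 50) = 2.009, so the floor is 2.009 × √(2/26) = 2.009 × 0.2774 = 0.557.

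With Bonferroni over 18 tests (assumed, to show the range), alpha per test is 0.05/18 = 0.00278 and the floor is 0.873. This exceeds the design effect of 0.8.

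**Step 3: mean reported d.** The t statistic was simulated with 1,000,000 draws per setting at n = 26 per group, and only significant results were kept. Apart from 0.8, the true values are assumptions that show the range.

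| True d | Share significant, alpha 0.05 | Mean reported d | Ratio to truth | Share of reported d above truth |
|---|---|---|---|---|
| 0.3 | 18.5% | 0.71 | 2.37 | 99.3% |
| 0.5 | 42.5% | 0.77 | 1.55 | over 99.9% |
| 0.8 | 80.7% | 0.91 | 1.14 | 62.6% |
| 1.0 | 94.2% | 1.05 | 1.05 | 53.7% |
| 1.2 | 98.9% | 1.23 | 1.02 | 51.3% |

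Under Bonferroni over 18:

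| True d | Share significant | Mean reported d | Ratio to truth |
|---|---|---|---|
| 0.5 | 10.3% | 1.02 | 2.04 |
| 0.8 | 40.7% | 1.09 | 1.37 |

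So an outcome with the planned effect of 0.8 would have no d reported in 100 − 80.7 = 19.3% of studies at unadjusted alpha, and in 100 − 40.7 = 59.3% under this correction.

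**Step 4: the same design without the filter.** If d is reported for every outcome, its mean is 0.31, 0.51 and 0.81 for true values of 0.3, 0.5 and 0.8, close to the truth. An outcome with observed d near 0 would carry a 95% CI of about ±0.56. This shows the reader how much the study leaves open.

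**The case against.** **Not every reported d is inflated.** A reader might infer that each published effect size overstates the truth. That does not follow: selection raises the average. At the plan's own d of 0.8 and unadjusted alpha, about 37% of significant estimates do not exceed the truth, and at a true d of 1.2 the mean is only 2% too high. Even under Bonferroni over 18, about 25% of significant estimates do not exceed a true d of 1.0.

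**Null outcomes are not left without any estimate.** A reader might also infer that nothing will be shown for them. The protocol does not say that means, SDs or test statistics will be withheld, and from these d can be computed. Correlations of S-EDE-Q, STAI and BMI with the Table 1 outcomes are planned without a significance condition. The Data Availability section promises the datasets. This stands, and it limits the point to standardised effect sizes for the group comparisons. It does not remove the point, because a table of d values drawn up under the rule would still be selected.

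**The figures rest on assumptions.** The true effects of 0.3 and 0.5 are not in the protocol, the multiplicity method is not named, and 26 is a minimum. The protocol foresees further recruitment after non-significant results, and a larger sample would lower the floor. All of this is fair, so the figures are given as a range.

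**It is only a reporting matter.** That is also true. But the article states the rule outright, so it is not a detail left to a fuller document.

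**Conclusion.** The point holds as a reporting weakness that should be corrected. Followed as written, the plan yields values of d that are too large on average, and it plans no standardised effect size for non-significant outcomes. At 26 per group the average excess at unadjusted alpha runs from about 14% (true d 0.8) to about 55% (true d 0.5) and more for smaller effects. A strict multiplicity correction makes it larger.

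These sizes assume independent groups with equal SDs, two-sided t-tests, n fixed at 26 per group and, for the upper figures, Bonferroni over 18 outcomes. The sample size and the validity of the tests are not affected.

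**What to change.** Replace the sentence on Cohen's d with: *The mean difference and Cohen's d (or a rank-based effect size for non-normal outcomes), each with its 95% CI, will be reported for every Table 1 outcome regardless of significance.*

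The cost is one sentence and one results table. It needs no new data and no further tests. The gain is a complete, unselected set of estimates. It does not protect a later reader who picks out only the significant outcomes and plans on those, so the results should present the 18 outcomes together.

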## Measures

### Psychometric measures

#### Eating disorder symptomatology

*Spanish Version of the Eating Disorder Examination Questionnaire (S-EDE-Q)* [36]. Composed by 28 7-point Likert-type response items ranging from 0 (not at all) to 6 points (markedly). Four subscales are measured, including dietary restraint, shape concerns, weight concerns, and eating concerns. The global score ranges from 0 to 6 points. As in Mond et al.’s [37], we will use a cut-off point ≥ 2.8 as clinically significant. Participants will be grouped according to this global index score.

To identify possible confounders, we will explore variables that may affect performance in eye movement tasks (premorbid intelligence and anxiety) [33]. Only those with significant relationships between groups will be deemed potential confounders and included in the analysis.

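### Pooled STAI correlations can reflect the group difference alone, because they are run across two groups formed on EDE-Q with no adjustment for group (minor)

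*Protocol article*

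**What the plan says.** All references are to the protocol article.

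- **Grouping.** Under Participants and procedure, the EDE-Q serves as a pre-screen, "allowing us to split the sample into two groups of participants". Once one group is full, only people who fall in the other are invited. Under Eating disorder symptomatology the cut-off is 2.8, and "Participants will be grouped according to this global index score".
- **Correlations.** Under Statistical analysis, Pearson correlations are run across groups and called exploratory: "correlation analyses will also be conducted between S-EDE-Q, STAI scores, and BMI and the outcome measures" in Table 1. No group term and no within-group analysis is stated.
- **Non-normal data.** The same section gives the group tests a non-parametric alternative. It gives the correlations none.
- **Multiplicity.** "We will apply a correction for multiple t-test comparisons" is the only stated correction, and "Alpha will be set at 0.05 for all analyses".
- **Anxiety.** It is a candidate confounder. If the groups differ significantly, it is to be added as a covariate to the group comparison.

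**The concern.** The pooled sample is close to a 50:50 mixture of two groups. In such a mixture, any two variables whose means both differ between groups are correlated overall, whether or not they are related within a group. The plan hypothesises group differences on the eye outcomes, and it treats anxiety as a variable that may differ by group. It deals with that possibility in the group comparison but not in the STAI correlations.

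SWJ rate together with anxiety is the study's secondary aim. A significant pooled STAI–eye correlation could therefore be taken to mean that eye movements vary with anxiety, when it may be only the group difference in another form. For EDE-Q the problem is different. The groups are that score cut in two, so the pooled correlation adds little to the group test and does not by itself show a graded relation with severity.

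**Working it through.** **The plan's own figure.** Under Sample size calculation, "An 80% of power analysis and a significant criterion of α = 0.05 were set", with d = 0.8. A two-sided independent two-sample t-test needs 25.52 per group, so 26. Power at 26 per group is 0.807. The stated N = 52 is reproduced. The plan gives no figure for the correlations.

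**Formula.** For two equal groups with zero within-group correlation, the correlation of a variable with group is d/√(d² + 4). The induced pooled r is the product of the two such terms.

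- Eye outcome at d = 0.8: 0.8/√4.64 = 0.371.
- Critical |r| at N = 52, two-sided 0.05: t(50) = 2.009, and 2.009/√(50 + 2.009²) = 0.273.

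**Results with the eye outcome at d = 0.8.** The group differences on the correlates are assumptions, since the document gives none. Rejection rates come from 40,000 simulated studies of 26 + 26 per setting, with normal data and no within-group association.

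| Correlate | Assumed d | Induced r | Pooled r significant |
|---|---|---|---|
| STAI | 0.5 | 0.371 × 0.243 = 0.09 | 10% |
| STAI | 1.0 | 0.371 × 0.447 = 0.17 | 22% |
| STAI | 1.2 | 0.371 × 0.514 = 0.19 | 28% |
| STAI | 1.5 | 0.371 × 0.600 = 0.22 | 37% |
| BMI | 0 | 0 | 5% |
| BMI | 0.2 | 0.371 × 0.100 = 0.04 | 6% |
| BMI | 0.5 | 0.371 × 0.243 = 0.09 | 10% |
| EDE-Q | 2.5 | 0.371 × 0.781 = 0.29 | 58% |
| EDE-Q | 3 | 0.371 × 0.832 = 0.31 | 64% |
| EDE-Q | 4 | 0.371 × 0.894 = 0.33 | 71% |

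A correlation adjusted for group (partial, 49 degrees of freedom) rejects in about 5% throughout. If the eye outcome does not differ by group, the pooled Pearson test also holds 5%.

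**Effect of balanced recruitment alone on the EDE-Q correlation.** Assume a linear population correlation of 0.20 or 0.30, with 10% to 20% of people above the cut-off. Filling the groups equally raises the pooled r to 0.22–0.24 or 0.32–0.35, which is a modest inflation.

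**Number of tests.** Table 1 gives 1 (fixation) + 5 (prosaccade) + 7 (antisaccade) + 5 (memory-guided) = 18 outcomes. With three correlates there are 18 × 3 = 54 tests. With state and trait STAI kept separate there are 18 × 4 = 72. If every null hypothesis holds, 54 × 0.05 = 2.7 to 72 × 0.05 = 3.6 false positives are expected.

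**The case against.** **Anxiety is already planned as a covariate.** A model with both group and anxiety would yield a group-adjusted anxiety slope, which is close to the remedy proposed here. This answers the point only in part. The step is triggered by a significant result, it serves the group comparison, and the pooled STAI correlations remain unadjusted.

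**The correlations are labelled exploratory.** The abstract and Discussion also call the study exploratory, and the Discussion treats the findings as a starting point for later work. Leaving hypothesis-generating tests uncorrected is common and defensible, so the multiplicity part is one of reporting. The label does not remove the pooling problem, which is bias and not chance.

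**EDE-Q.** A reader might take the 58% to 71% as false-positive rates. They are not. Group is EDE-Q dichotomised, so an eye outcome that differs by group really is associated with EDE-Q. What remains is redundancy with the group test. Adjusting for group also removes much of the EDE-Q signal, so it cannot simply replace the pooled value.

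**BMI.** A reader might extend the artefact to BMI. The groups are not selected on it, and everyone lies between 18.5 and 24.9, so there is no reason in the document to expect more than a small effect.

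**Pearson coefficients.** Normality and outliers are to be checked, the outcome distributions are unknown, and no harm has been quantified. The missing rank alternative is a small inconsistency with the group tests.

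**Conclusion.** The point holds in a limited form and is minor. Following the plan as written can produce a STAI–eye correlation with no association inside either group: r of about 0.09 to 0.22, significant in about 10% to 37% of studies against 5% after adjustment for group. This requires both variables to differ by group. It rests on the plan's d = 0.8 for the eye outcome, an assumed anxiety difference of d = 0.5 to 1.5, normal data, and reading the across-groups wording as pooled.

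The pooled EDE-Q correlation is not spurious, but it is largely a second view of the group comparison. The document does not support a claim that pooling manufactures associations for all three correlates, or that uncorrected exploratory p-values are in themselves an error.

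**What to change.** Amend the correlation sentence under Statistical analysis as follows:

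1. Report group-adjusted STAI correlations (partial, or pooled within-group) beside the pooled values.
2. Label the pooled EDE-Q correlation as including the group difference, and show the group-adjusted value as a supplement.
3. Use a rank-based coefficient where the planned normality check fails, to match the group tests.
4. Give estimates with 95% confidence intervals. Either control the false discovery rate over this family or state the number of tests (54 or 72) and that the p-values are uncorrected and exploratory.

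The cost is a few lines of text and no new data. The one downside is that group-adjusted EDE-Q correlations lose range and power, so they should stand beside the pooled value and not replace it.

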### Study objectives and hypothesis

As Malcom and Phillipou [18] noted in their recent review, demonstrating a relationship with illness is one of the first steps in determining biomarkers and endophenotypes. As illustrative example, first Phillipou et al. [33] showed the existence of specific eye movement anomalies in patients with AN and only after these findings, they amplified the scope of their study and were able to identify the state-independence of these eye movement abnormalities [32]. Following this line of reasoning, we will investigate whether the aforementioned eye movement abnormalities detected are, in this case, associated in young-adult women with subclinical symptomatology. Therefore, this study will take as primary aim to investigate whether participants with subclinical ED symptomatology and control participants differ in their performance on a range of eye movement tasks. We hypothesize that participants with subclinical ED symptomatology compared to controls would be prone to show shorter saccade latencies and more inhibitory errors in a prosaccade/antisaccade task and in a memory-guided saccade task, respectively, and an increased rate of SWJs in a fixation task. Additionally, as secondary aim, and following the same approach of Phillipou et al. [31, 32], we will test the potential role of SWJ rate and anxiety for discriminating the different groups tested in our study (participants with subclinical ED symptomatology vs. control participants).

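### The secondary aim is analysed only if anxiety and square wave jerk rate are both significant, and the single joint accuracy planned does not show what the eye-movement measure adds to anxiety

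*Protocol article*

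**What the plan says.** Study objectives and hypothesis sets the secondary aim without a condition: "we will test the potential role of SWJ rate and anxiety for discriminating the different groups". The Discussion repeats it as a test of the accuracy of the two measures.

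The Statistical analysis section adds a condition. The analysis is done "if significant differences are found between STAI scores and SWJ rate", and then "a discriminant analysis will be performed on the entire sample to elucidate to what extent both measures correctly classify group membership". No model with one measure alone is mentioned, and the text does not say whether accuracy is cross-validated.

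The same section corrects the t-tests for multiplicity and adds anxiety and premorbid intelligence as covariates where the groups differ. It also states: "Alpha will be set at 0.05 for all analyses". Sample size calculation plans for "a minimum sample of 26 participants in each group", based on d = 0.8 and 80% power. The Background reports that the cited work reached a joint accuracy of at least 70%.

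**The concern.** There are three difficulties, in order of weight.

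- **The condition conflicts with the aim.** How well two measures classify is an estimation question, and it has an answer whether or not each measure is significant. Under the condition, the aim is answered only in studies where both observed differences are large. Accuracy is then estimated in a selected set of studies.
- **The target is joint only.** The protocol treats anxiety as a confounder, yet the Discussion is interested in eye-tracking measures as screening tools. One accuracy for the pair does not say how much comes from SWJ rate, so a result near the cited 70% could be read as support for SWJ rate when anxiety supplies most of it.
- **The trigger is mis-worded.** A difference between a questionnaire score and an eye-movement rate is not a group comparison. The workable reading is that each measure differs between the groups, and this reading is used below.

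**Working it through.** **Inputs from the protocol article:** 26 per group, d = 0.8, 80% power, alpha 0.05. Sidedness is not stated.

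**Assumptions, not in the document:** the true d for STAI and for SWJ rate, their within-group correlation r, normal data, and a condition applied at uncorrected two-sided p < 0.05.

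**Step 1. The plan's own figure.** The noncentrality is d × √(n/2) = 0.8 × √13 = 2.884 on 50 degrees of freedom. Two-sided power is 0.807 at 26 per group and 0.791 at 25, so 26 per group is reproduced.

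**Step 2. How often the condition is met.**
- Both d = 0.8, r = 0: 0.807 × 0.807 = 0.652. Simulation gave 0.658, and 0.690 at r = 0.3. The aim is therefore dropped in about 31% to 35% of studies.
- STAI d = 1.2, SWJ d = 0.4, r = 0.3: 0.300 by simulation.
- STAI d = 1.0, SWJ no effect: 0.942 × 0.05 = 0.047.
- Neither measure differs: 0.05 × 0.05 = 0.0025, or about 0.3%.

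A multiplicity correction applied to the condition would lower all of these.

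**Step 3. Accuracy when the condition is met.** A two-predictor linear discriminant was simulated at 26 per group. The last column is the normal-theory accuracy of STAI alone, Φ(d/2).

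| Assumed STAI d / SWJ d / r | Condition met | Joint, fitting data | Joint, new data | Gap (points) | STAI alone |
|---|---|---|---|---|---|
| 0.8 / 0.8 / 0 | about 65% | 74.4% | 70.8% | 3.6 | 65.5% |
| 0.8 / 0.8 / 0.3 | about 69% | 72.7% | 68.8% | 3.9 | 65.5% |
| 1.2 / 0.4 / 0.3 | about 30% | 75.7% | 71.4% | 4.3 | 72.6% |
| 1.0 / 0 / 0 | about 5% | about 73% | about 65% | about 8 | 69.1% |

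**Step 4. What the joint figure hides.** The first and third rows give similar joint accuracies on the fitting data (74.4% and 75.7%), but they mean different things. In the first, SWJ rate adds about 5 points on new data (70.8 − 65.5 = 5.3). In the third it adds nothing. The squared distance between groups is D² = (1.44 + 0.16 − 2 × 0.3 × 1.2 × 0.4)/(1 − 0.09) = 1.312/0.91 = 1.442, so D = 1.201. Best possible joint accuracy is then Φ(0.600) = 72.6%, the same as STAI alone. In simulation STAI alone gave about 73% on new data and 74% on the fitting data. So even a real group difference in SWJ rate need not improve classification.

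**Step 5. Cross-validation alone is not enough.** With STAI d = 0.8 and SWJ d = 0, leave-one-out accuracy without the condition is 64.8% against 64.5% on new data. After the condition it is 69.7% against 61.8%, because the selection lies outside the cross-validation.

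**The case against.** A reader might infer that the plan will commonly report 70% or more while SWJ rate does nothing. The document does not support this. With STAI d = 1.0 and no SWJ effect, joint accuracy on the fitting data does average about 70%, but that is an average over all studies, and the plan would run the analysis in only about 5% of them. About half of those passes would have SWJ rate differing in the direction opposite to the hypothesis. The same applies to the 57% against 50% found when neither measure differs: the condition is then met in about 0.3% of studies. Against this particular error the condition gives real protection.

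A reader might also infer that accuracy is certainly scored on the fitting data. The phrase about the entire sample may mean only that both groups are pooled. Leave-one-out classification is not excluded, and an article may leave that choice to a fuller document. The gaps in the table therefore apply only if resubstitution is meant.

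Nor does the plan ignore SWJ rate beyond anxiety. If the groups differ, the comparison is repeated with anxiety as a covariate, so it goes too far to say that the study cannot show anything about SWJ rate. The study is also described as exploratory, and the aim names the two measures together.

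These points limit the size of the problem but do not remove it. The condition and the joint-only target are stated in the text, not left to another document. The adjusted comparison concerns a mean difference and gives no accuracy figure.

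**Conclusion.** The point holds, with moderate confidence. As written, the plan can leave its secondary aim unanalysed: in about a third of studies if both measures have d = 0.8, and in about 70% if STAI d = 1.2, SWJ d = 0.4 and r = 0.3, before any multiplicity correction. When the analysis does run, the joint accuracy does not show what SWJ rate adds to anxiety.

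Optimism from same-data scoring is secondary and depends on that reading. It is about 4 points in the scenarios with real effects in both measures, and about 8 points in the roughly 5% of studies where an ineffective SWJ rate passes by chance. For scale, the standard error of a 70% accuracy on 52 women is √(0.7 × 0.3/52) = 0.064, or about 6 points.

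The sizes rest on assumed effects, normal data and the reading of the trigger as a group difference in each measure. The conflict between the unconditional aim and the conditional analysis needs none of these assumptions. The primary group comparisons are not affected.

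**What to change.** - Run the discriminant analysis on all analysed participants whatever the results of the group tests, and delete the condition. If a condition is kept for another purpose, word it as a difference between groups in each measure.
- Report accuracy for three models: STAI alone, SWJ rate alone, and both. Base any claim about SWJ rate on the gain of both over STAI alone.
- State that accuracy is leave-one-out cross-validated and give 95% confidence intervals. If resubstitution accuracy was intended, replace it.

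The cost is two extra model runs on data already collected. The reported accuracy will be slightly lower, and with a standard error of about 6 points at N = 52 its interval will be wide. The gain over STAI alone should be described as exploratory.
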